### Power analysis

Power to detect an experimental effect is based on *n* = 288 audiotaped sessions coded. The study is optimally powered (exceeding .80) to detect a between-condition effect size of *d* = .30 (small) or greater when data are combined across sites. Power calculations were conducted using Optimal Design 3.01 [40]. With nested designs, power is substantially affected by number of sites as well as clusters (therapists and clients) within site [41], and less so by cases (sessions) within cluster. Aggregating across site, and assuming 32 therapists (*unit of randomization*) treating 6 clients each and submitting 1.5 taped sessions for review (*unit of analysis*) and moderately sized within-cluster intraclass correlation coefficients (ICCs) (*ρ* = .05) [42], yields optimal levels of power (exceeding .80) for even small effects (*d* = .30) and increasing power (exceeding .90) with effect sizes of *d* = .40 and greater. Previous research has yielded effect sizes *d* = .40–.50 using a similar design [43].

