### Data analysis plan

Study data will have a three-level nested structure: clients within therapists within sites (we will average across sessions for each client). The basic analytic approach for these nested data will be multilevel mixed effects models examining the effects of Phase (Baseline versus Implementation) and Condition (Training Only versus Training + Feedback + Consultation) on dependent variables aggregated across each time period: 4-month Baseline phase (prior to MTFS-I training) and 12-month Implementation phase. We will use maximum likelihood estimation for continuous variables and robust weighted least squares for categorical variables. We will model Site and Therapist as random effects in all models. We will include Therapist (age, sex, race/ethnicity, experience, EBT attitudes, EBT proficiency) and Client (age, sex, race/ethnicity) factors at their respective levels to examine potential effects. Effect sizes will be calculated using the standardized *d* effect size indicator, interpreted as the standardized difference between contrasts for Phase and Condition comparisons [41]. Aim 1 exploratory contrasts will examine the Phase (within-subjects) effect, contrasting Baseline versus Implementation across all sites in EBT self-monitoring (reliability, accuracy) and EBT technique use (averaging across FT and CBT techniques). Aim 2 will experimentally test the Condition (between-subjects) effect on MTFS-I uptake, EBT self-monitoring, and EBT technique use.

To analyze EBT self-monitoring, reliability between therapists and observers on FT and CBT technique use will be calculated using the ICC_2,2_ [44]. Conditions will be compared on the relative magnitude of ICCs for each EBT scale. To compare conditions on therapist accuracy, we will use statistical equivalence testing methods, applying the confidence interval approach [45] to examine whether therapist scores are equivalent to corresponding observer scores. To analyze EBT technique use, a series of multilevel mixed effects models will be conducted with a dummy-coded Condition variable included at the Therapist level to test the contrast of main interest; alpha will be adjusted to account for multiple contrasts. For the Aim 1 analyses of Phase contrasts, a product interaction terms will be included to examine Phase by Condition effects; for significant interactions, we will test simple effects by examining Phase contrasts separately within condition.

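### Power is stated for 288 taped sessions, but the analysis uses one averaged score per client (192); the planned analysis does not reach the stated power, though the change of unit explains only a small part of the gap

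*Protocol article*

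**What the plan says.** The protocol article's Power analysis section opens with "Power to detect an experimental effect is based on *n* = 288 audiotaped sessions coded". Its inputs are given as "assuming 32 therapists (*unit of randomization") and "treating 6 clients each and submitting 1.5 taped sessions for review", the session being labelled the unit of analysis, with "moderately sized within-cluster intraclass correlation coefficients (ICCs) (*ρ* = .05"). From these it claims power "exceeding .80) to detect a between-condition effect size of *d* = .30 (small) or greater when data are combined across sites", and power above .90 from d = .40 upward. The same section acknowledges that "power is substantially affected by number of sites as well as clusters (therapists and clients) within site".

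The Data analysis plan section describes the structure as "clients within therapists within sites (we will average across sessions for each client"), with Site and Therapist as random effects. The lowest unit in the model is therefore the client mean. The section on observational coding projects 192 clients at 1.5 selected recordings each, which is where the 288 comes from.

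**The concern.** The two sections name different units for the same contrast. The power statement counts 288 sessions; the model will see 192 client scores. The single ICC of .05 is not tied to a level, so a reader cannot tell whether the likeness of two tapes from one client has been allowed for. The scale of d is also open: a standardized difference in session scores is not the same quantity as one in client averages.

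What is at stake is how the Aim 2 comparison of conditions will be read. If the analysis that is run has much less power than stated, a null result could be taken as evidence against feedback plus consultation when the trial had little chance of detecting a small effect.

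**Working it through.** **Inputs from the article.** 32 therapists; 6 clients per therapist; 1.5 tapes per client; so 6 × 1.5 = 9 tapes per therapist, 32 × 9 = 288 tapes and 32 × 6 = 192 clients. ICC = .05. Claimed power: over .80 at d = .30 and over .90 at d = .40.

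**Assumptions, because the article gives no figure.** 16 therapists per condition; alpha .05 two-sided; noncentral t with 32 − 2 = 30 df; the ICC of .05 is at therapist level; half of each therapist's clients have one tape and half have two (3 + 3, which averages 1.5). The client-level share of session variance, rc, is varied from 0 to .50.

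**Formula.** With v the variance of a therapist mean, SE = √(4v/32) and the noncentrality is d/SE.

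**Step 1: the article's own figure, at the session unit.** v = .05 + .95/9 = .1556, so SE = .1394.
- d = .30: noncentrality 2.15, power .549 (normal approximation .576).
- d = .40: noncentrality 2.87, power .793 (normal approximation .818).

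The claimed figures do not reproduce. Even with clustering ignored altogether (144 sessions per arm), the normal approximation gives only .721 at d = .30, although it does give .924 at d = .40.

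**Step 2: the planned client average, d on the session scale.** A client mean has within-therapist variance rc + (.95 − rc) for one tape and rc + (.95 − rc)/2 for two. The average over the 3 + 3 split is rc + .75(.95 − rc), so v = .05 + [rc + .75(.95 − rc)]/6.
- rc = 0: v = .1687; power .516 at d = .30 and .760 at d = .40.
- rc = .50: v = .1896; power .471 and .710.

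**Step 3: the planned client average, with d and the ICC on the client-mean scale.** v = .05 + .95/6 = .2083, so SE = .1614. Power is .436 at d = .30 and .670 at d = .40; power of .80 needs d of about .47.

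**Step 4: what the change of unit costs by itself.** Here d stays on the session scale, and a session model with a client random intercept is compared with equally weighted client means. The session model gives v = .05 + 1/[3/.95 + 3/(rc + (.95 − rc)/2)].

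| rc | session model, d = .30 | client means, d = .30 | difference |
|---|---|---|---|
| 0 | .549 | .516 | .033 |
| .10 | .530 | .506 | .024 |
| .30 | .500 | .488 | .012 |
| .50 | .476 | .471 | .005 |

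At d = .40 the difference runs from .793 − .760 = .033 down to .716 − .710 = .006.

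**The case against.** The strongest reply is that the mismatch is mostly a matter of wording. Both sections describe the same therapist-level contrast on the same tapes. In a therapist-randomized design the number of therapists dominates, and averaging within client is a legitimate, common analysis. Step 4 bears this out, and that part of the reply stands.

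Two stronger readings are tempting, and the article does not support either.
- A reader might infer that the power calculation leaves clients out. It does not: the section names therapists and clients as clusters, counts 6 clients per therapist and speaks of ICCs in the plural. What can be said is that one value is given and its level is not.
- A reader might take the fall from .55 to .44 at d = .30 as the price of averaging. That comparison also moves d and the ICC to another scale. Averaging shrinks the standard deviation, so a session-scale d of .30 corresponds to about .32 to .34 on the client-mean scale for rc from .50 to 0. The .44 therefore describes a smaller true effect. It is still a possible reading of the plan, because the Data analysis plan computes standardized effects from models of averaged scores, but it does not measure what averaging loses.

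The reply does not rescue the stated power. An article may leave detail to a fuller document, but here it states two units that disagree and a power figure that its own inputs do not give under either.

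**Conclusion.** The inconsistency is real and should be corrected. For the client-average analysis that is planned, power is about .47 to .52 at d = .30 and .71 to .76 at d = .40 on the session scale, or about .44 and .67 on the client-mean scale, against the stated figures of over .80 and over .90. The change of unit accounts for only about 0.5 to 3 points of this. Most of the shortfall is already present at the session unit, where the article's inputs give .55 and .79.

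These figures rest on the assumed equal allocation, two-sided .05, 30 df, therapist-level ICC, 3 + 3 tape split and range of client-level ICCs. The plan says alpha will be adjusted for multiple contrasts, which would lower power further.

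**What to change.** Name one unit and use it in both the Power analysis and the Data analysis plan. State which level the ICC of .05 refers to, and whether d is standardized on session scores or client means. Then restate power, or the detectable d, for the analysis that will be run, over a range of client-level ICCs and with the alpha and sidedness written out.

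Keeping the client averages is acceptable. Analysing coded sessions with a client random intercept within therapist is also acceptable: it uses every tape and weights one-tape and two-tape clients properly, but the gain is at most about 3 points, so it is optional.

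The cost is a few reworded sentences and a recalculation. The article reports no enrolment yet, so nothing collected is affected. The downside is that the published power becomes clearly less favourable.

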### Data analysis plan

Study data will have a three-level nested structure: clients within therapists within sites (we will average across sessions for each client). The basic analytic approach for these nested data will be multilevel mixed effects models examining the effects of Phase (Baseline versus Implementation) and Condition (Training Only versus Training + Feedback + Consultation) on dependent variables aggregated across each time period: 4-month Baseline phase (prior to MTFS-I training) and 12-month Implementation phase. We will use maximum likelihood estimation for continuous variables and robust weighted least squares for categorical variables. We will model Site and Therapist as random effects in all models. We will include Therapist (age, sex, race/ethnicity, experience, EBT attitudes, EBT proficiency) and Client (age, sex, race/ethnicity) factors at their respective levels to examine potential effects. Effect sizes will be calculated using the standardized *d* effect size indicator, interpreted as the standardized difference between contrasts for Phase and Condition comparisons [41]. Aim 1 exploratory contrasts will examine the Phase (within-subjects) effect, contrasting Baseline versus Implementation across all sites in EBT self-monitoring (reliability, accuracy) and EBT technique use (averaging across FT and CBT techniques). Aim 2 will experimentally test the Condition (between-subjects) effect on MTFS-I uptake, EBT self-monitoring, and EBT technique use.

To analyze EBT self-monitoring, reliability between therapists and observers on FT and CBT technique use will be calculated using the ICC_2,2_ [44]. Conditions will be compared on the relative magnitude of ICCs for each EBT scale. To compare conditions on therapist accuracy, we will use statistical equivalence testing methods, applying the confidence interval approach [45] to examine whether therapist scores are equivalent to corresponding observer scores. To analyze EBT technique use, a series of multilevel mixed effects models will be conducted with a dummy-coded Condition variable included at the Therapist level to test the contrast of main interest; alpha will be adjusted to account for multiple contrasts. For the Aim 1 analyses of Phase contrasts, a product interaction terms will be included to examine Phase by Condition effects; for significant interactions, we will test simple effects by examining Phase contrasts separately within condition.

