**Fig. 2 Fig2:**
[figure not shown]
SPIRIT diagram depicting the schedule of trial enrollment, interventions, and assessments

To host trial activities we will recruit four behavioral health outpatient clinics that attest to endorsing FT and CBT as staples of their clinical practice. All full-time clinicians will be eligible to participate. We project to enroll 32 therapists total (8 therapists per site [6 active slots plus 2 to replace dropouts]) treating 192 cases (24 therapist slots × 8 consenting cases/year). Treatment will average ~ 6 sessions/case (given routine therapy attrition), yielding ~ 1152 post-session therapist-reported checklists, about half with accompanying recordings (*n* ~ 576); half of these (~ 288 sessions) will be coded for EBT fidelity by research staff. Figure 3 shows a Consolidated Standards of Reporting Trials (CONSORT) flow chart of projected study enrollment. We will randomize volunteer therapists within each site to study condition at the start of the Implementation phase, given that MTFS-I procedures target individual therapists and their supervisors rather than entire agencies [24]. We will not randomize supervisors to condition, for two reasons. Because therapists in the Training Only condition will engage in solitary online training activities and will not review feedback reports or participate in expert consultation meetings with supervisors, we do not anticipate substantial supervisor “crossover” effects should a given supervisor oversee therapists in both conditions. Also, many clinics have only one supervisor, making it neither practical nor ecologically valid to randomize supervisors into condition. To guard against experimental contamination, supervisors will be asked not to review feedback reports in the presence of Training Only therapists.

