#### EBT fidelity and MTFS-I uptake data collection

ITT-ABP checklists and session audio recordings will be collected at all sites during the Baseline and Implementation phases. During the Implementation phase, therapists and supervisors will complete online MTFS-I training activities (self-monitored learning modules, mock vignette coding). To assess between-condition differences in consultation activities, therapists in both conditions will report on the extent to which training materials and feedback reports are discussed during clinical supervision.

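### Between-condition power is computed on 288 sessions, but the analysis uses client averages and the 288 is not divided between Baseline and Implementation

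*Protocol article*

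**What the plan says.** All references are to the protocol article.

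- **Power analysis:** "Power to detect an experimental effect is based on *n* = 288 audiotaped sessions coded". The inputs are given as "assuming 32 therapists (*unit of randomization*) treating 6 clients each and submitting 1.5 taped sessions for review (*unit of analysis"), with an ICC of .05. The design is called "optimally powered (exceeding .80) to detect a between-condition effect size of *d* = .30 (small) or greater", with "increasing power (exceeding .90) with effect sizes of *d* = .40 and greater".
- **Data analysis plan:** the nested structure is "clients within therapists within sites (we will average across sessions for each client"). The levels are client, therapist and site; there is no session level. Dependent variables are aggregated over each of the two phases, 4 months and 12 months long.
- **Trial design, sample-size paragraph after Figure 2:** the trial projects "treating 192 cases (24 therapist slots × 8 consenting cases/year"). Therapists are randomized at the start of the Implementation phase.
- **Observational coding of EBT delivery:** one Early (sessions 1–3) and one Later (session 4 onward) recording is drawn per client. This is projected at 1.5 recordings for each of 192 clients, or 288.
- **EBT fidelity and MTFS-I uptake data collection:** "ITT-ABP checklists and session audio recordings will be collected at all sites during the Baseline and Implementation phases".

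No shown text divides the 192 clients or the 288 recordings by phase.

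**The concern.** Two features of the data behind the Aim 2 power figure do not match the data that the Condition model will use.

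The first is the unit. Power is computed on sessions, while the model is fitted to client values. The number of observations differs (288 against at most 192). So does the meaning of d, because a standardized difference on client means is not the same quantity as one on single sessions.

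The second is the phase. Recordings made before randomization carry no exposure to either condition. If some of the 288 are Baseline recordings, they do not count toward the Condition sample. If none are, the recordings needed for the Aim 1 Baseline comparison are outside the stated workload. The text does not say which.

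At stake is whether the trial can detect the small effect it says it can, and whether the coding effort is budgeted correctly.

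**Working it through.** **Counts.** 24 × 8 = 192 clients; 192 × 1.5 = 288 recordings; 32 × 6 × 1.5 = 288 sessions. The projection and the power inputs agree on the total.

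**Inputs.** From the document: J = 32 therapists, 9 sessions each (6 × 1.5), ρ = .05 (level not stated), d = .30 and .40. Assumed: two-sided alpha .05 without the multiplicity adjustment that the plan mentions (which would lower power), and 16 therapists per condition.

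**Formula.** Var(difference) = 4[ρ + (1 − ρ)/m]/J, with m observations per therapist. Power is from a noncentral t with J − 2 = 30 df; the normal approximation is in brackets.

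**Step 1: the plan's own figure, all 288 sessions (m = 9).** Design effect 1 + 8 × .05 = 1.40; effective n = 288/1.40 = 205.7. Var = 4(.05 + .95/9)/32 = .01944; SE = .1394.
- d = .30: .55 [.58], against more than .80 stated.
- d = .40: .79 [.82], against more than .90 stated.
- Effect detectable with 80% power: d = .40 [.39].

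The stated power is not reproduced. Ignoring clustering altogether, 288 sessions give [.72] and [.92], so .80 at d = .30 is still not reached two-sided.

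**Step 2: the two readings of 288.**
- *288 covers both phases.* With even accrual over 4 + 12 = 16 months (assumption), Implementation holds 288 × 12/16 = 216 sessions and 192 × 12/16 = 144 clients; Baseline holds 72 sessions.
- *288 is the Implementation year.* At the same rate the 16-month total is 192 × 16/12 = 256 clients and 256 × 1.5 = 384 recordings, so 96 Baseline recordings are not in the projection.

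**Step 3: Condition power on the first reading (m = 216/32 = 6.75).** Var = 4(.05 + .95/6.75)/32 = .02384; SE = .1544.
- d = .30: .47 [.49]. d = .40: .71 [.74]. Detectable d = .45 [.43].

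The loss due to phase is .55 − .47 = .08 at d = .30 and .79 − .71 = .08 at d = .40.

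**Step 4: the cost of averaging, with d kept on the session scale.** Take 6 clients per therapist, half with one session and half with two, a therapist variance share of .05 and a client share of .05 to .50 (assumed). The variance of a therapist's mean is:

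| Client share | Client averages, equal weight | Sessions, equal weight | Change |
|---|---|---|---|
| .05 | .05 + .05/6 + .90 × .75/6 = .1708 | .05 + .05 × 15/81 + .90/9 = .1593 | +7% |
| .20 | .05 + .20/6 + .75 × .75/6 = .1771 | .05 + .20 × 15/81 + .75/9 = .1704 | +4% |
| .50 | .05 + .50/6 + .45 × .75/6 = .1896 | .05 + .50 × 15/81 + .45/9 = .1926 | −2% |

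The SE of the Condition difference is the square root of 4/32 times these values. At d = .30 the normal-approximation power is [.54] for averages against [.57] for sessions at a client share of .05, and [.50] against [.49] at .50. Averaging therefore changes power by about .03 at most.

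Only if d = .30 is redefined on client means does the drop become larger: 192 clients at ρ = .05 give .44 [.46] at d = .30 and .67 [.70] at d = .40; 144 clients give .36 [.38] and .57 [.60].

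**The case against.** The best defence concerns phase. The 192 is built from cases per year, the Implementation phase lasts one year, and the power paragraph ties 288 to the experimental effect. On that reading 288 is the right number of sessions for the Condition contrast, and the cut to 216 does not apply. This is a fair reading, and the enrollment figure, which is not shown, may settle it. It leaves the Baseline recordings outside the projected total, and it does not rescue the stated power, which falls short with all 288 sessions.

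Client means are also a legitimate unit of analysis. That stands: the defect is that two sections name different units, not that averaging is wrong.

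A reader might infer more than the document supports:

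- *That the whole shortfall from .80 comes from unit and phase.* It does not; .55 is already the figure before either correction.
- *That Aim 1 has no planned coded Baseline sessions.* Recordings are collected in Baseline and selected for coding for each client. They may be missing from an approximate total, which is not the same as missing from the plan.
- *That a client treated across the phase boundary has Baseline and Implementation sessions pooled.* Dependent variables are to be aggregated within each period, which on its plain reading prevents this.
- *That the Phase contrast carries a treatment-stage bias of a known size.* A short Baseline probably holds relatively fewer Later sessions. The document gives no session frequency by phase and no stage effect on technique use, so no size can be derived.

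**Conclusion.** The concern holds in two textual respects. The Power analysis and the Data analysis plan name different units of analysis, and the projection of 192 clients and 288 recordings is not divided by phase although only post-randomization data inform the Condition contrast.

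The added cost from phase is about .08 in power, and only if 288 spans both phases with even accrual. The cost of averaging is small while d stays on the session scale. The stated power at d = .30 and d = .40 is reached on neither reading under the document's own ICC with two-sided alpha .05 and equal allocation. Most of that gap is already present before the unit or phase is corrected, so correcting these alone will not restore the stated figures. Adjusting for therapists' Baseline data could recover some precision, but the power statement does not claim it.

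**What to change.** 1. Use one unit of analysis in the Power analysis and Data analysis plan sections, and state the scale of d, the level of the ICC, alpha and sidedness.
2. State projected coded sessions and clients separately for Baseline and Implementation.
3. Restate the Condition power, or the detectable effect, on Implementation-phase data only. On the assumptions above the detectable d is about .40 with 288 Implementation sessions and about .45 with 216.
4. As an inexpensive addition, analyse coded sessions with random effects for client and therapist and an Early/Later fixed effect, because sampling is already stratified by stage.

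Items 1 to 3 are changes of wording and a recalculation; item 4 enlarges the model slightly. No further coding is needed if 288 covers both phases. If 288 is the Implementation year alone, Baseline coding must be budgeted (about 96 recordings at the same accrual rate). The stated power will become less favourable. The article reports that enrolment had not begun, so the correction could be made before data collection.

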## Methods/design

### Trial design

The trial design is a two-group randomized trial with baseline comparison: Following a 4-month Baseline phase, therapists working in behavioral health treatment sites will be randomized across two experimental conditions, Training Only versus Training + Feedback + Consultation, for a 1-year Implementation phase. During both study phases we will collect EBT fidelity data (therapist-reported checklists, session audiotapes); during the Implementation phase we will also collect MTFS-I uptake data (training and consultation activity). In Aim 1, by comparing Baseline versus Implementation data, we can examine the effectiveness of the MTFS-I training component for enhancing EBT fidelity across study sites, yielding proof-of-concept data in accord with the well-established Stage Model of behavioral treatment development [27]. In Aim 2, by experimentally comparing Training Only versus Training + Feedback + Consultation, we can test the added value of MBC procedures combined with expert consultation procedures [26] for enhancing MTFS-I benefits. Also the quasi-experimental analysis of Baseline data (averaged across all study therapists) versus Training Only condition data will shed light on the unique effects of the online training component, which is the most pragmatic feature of the overall MTFS-I package. Comparing averaged Baseline-phase data versus the Training + Feedback + Consultation condition will also provide insight on the full MTFS-I effects. It was not possible to include a no-intervention or waitlist control group because sites unilaterally preferred that all study therapists receive a clinically meaningful training experience. To maximize clinical utility and trainee motivation, each study therapist will select whether they want to train in FT, CBT, or both; training in both approaches will double the time commitment (to approximately 40 total min per week) for the given trainee. Figure 2 is the Standard Protocol Items: Recommendations for Interventional Trials (SPIRIT) diagram depicting the schedule of trial enrollment, interventions, and assessments. Additional file 3 presents the SPIRIT checklist. Study sites and eligibility, sample size, randomization, and contamination procedures.

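### The Aim 2 test of technique use omits the therapist's Baseline-phase value of the outcome and is not restricted to Implementation-phase data, so a diluted Condition effect is possible

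*Protocol article*

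**What the plan says.** On data collection, Trial design states: "During both study phases we will collect EBT fidelity data (therapist-reported checklists, session audiotapes". The same section places randomization at the start of the Implementation phase, so Baseline-phase outcomes are pre-randomization measurements.

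On the randomized comparison, the Data analysis plan states: "Aim 2 will experimentally test the Condition (between-subjects) effect on MTFS-I uptake, EBT self-monitoring, and EBT technique use". For technique use, the test is carried by a dummy variable for Condition at therapist level.

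On covariates, the same section states: "We will include Therapist (age, sex, race/ethnicity, experience, EBT attitudes, EBT proficiency) and Client (age, sex, race/ethnicity) factors at their respective levels". The Baseline-phase outcome is not in that list.

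On the model, the basic approach names both Phase and Condition as effects, with outcomes aggregated within the 4-month and 12-month periods. The product of Phase and Condition is introduced for the Aim 1 Phase contrasts, which are labelled exploratory. The section does not say whether the Aim 2 Condition model uses rows from one phase or both.

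In Protocol summary and specific aims, the randomized comparison is described as one of the gain in fidelity under each condition.

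**The concern.** The therapist's own earlier technique use is a natural covariate for later technique use, and the trial already pays to collect it. The listed EBT proficiency covariate does not replace it. Study measures defines proficiency as therapists' own judgement of their allegiance and skill, and the Background reports that therapists rate their EBT use well above what observers see.

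The second issue is which data the Condition coefficient summarizes. Before randomization the expected difference between conditions is zero. A Condition main effect fitted to both phases, with no product term, averages that zero with the Implementation-phase effect and so understates it. The only planned term that ties the randomized comparison to change from Baseline sits under Aim 1.

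At stake are some precision (from the missing adjustment) and, on one permitted reading of the model, a substantial part of the effect that the trial is meant to estimate.

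**Working it through.** **Inputs from the Power analysis section.** "Power to detect an experimental effect is based on *n* = 288 audiotaped sessions coded"; "assuming 32 therapists (*unit of randomization*) treating 6 clients each and submitting 1.5 taped sessions for review", that is 6 × 1.5 = 9 sessions per therapist; "moderately sized within-cluster intraclass correlation coefficients (ICCs) (*ρ* = .05". Phase lengths of 4 and 12 months (1:3) come from the Data analysis plan.

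**Assumptions not in the article.** Two-sided alpha of .05 before any adjustment (the article says only that "alpha will be adjusted to account for multiple contrasts"); 1:1 allocation; the same therapist effect in both phases; coded sessions proportional to phase length; all 32 therapists contributing to both phases; therapist ICCs (ρ) above .05.

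**Step 1: the plan's own figure.** The claim is: "The study is optimally powered (exceeding .80) to detect a between-condition effect size of *d* = .30 (small) or greater". The design effect is 1 + (9 − 1) × .05 = 1.40, and 288 / 1.40 = 205.7 effective sessions. Power at d = .30 is then .576 (normal), or .549 from a t test on therapist means with 30 df. The stated figure is not reproduced. That is a separate matter; these values serve here only as the reference.

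**Step 2: dilution if both phases are pooled.** With effect d in Implementation, 0 at Baseline and no product term, the Condition coefficient estimates w × d, where w is the weight on Implementation.
- Data split 1:3: w = .75, and .75 × .30 = .225.
- Phases weighted equally (one aggregate per period): w = .50, and .50 × .30 = .15.

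A closed-form generalized least squares calculation with a random therapist intercept gives the same .225 and .15 at ρ = .05, .20 and .50.

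Power at true d = .30 and ρ = .05:

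| Coded sessions | Implementation only | Pooled, 1:3 | Pooled, equal weights |
|---|---|---|---|
| (A) 288 over both phases (72 + 216) | .468 | .346 | .156 |
| (B) 288 in Implementation plus 96 at Baseline | .549 | .403 | .181 |

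**Step 3: gain from Baseline adjustment.** In (A) a therapist has 72 / 32 = 2.25 Baseline and 216 / 32 = 6.75 Implementation sessions. The correlation r between the two phase means satisfies

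r² = ρ² / {[ρ + (1 − ρ)/6.75] × [ρ + (1 − ρ)/2.25]}.

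Adjustment multiplies the variance of the contrast by 1 − r², which is worth 1/(1 − r²) times as many therapists.
- ρ = .05: r² = .0025 / (.1907 × .4722) = .028, worth about 3% more therapists.
- ρ = .20: r² = .04 / (.3185 × .5556) = .226, worth 29% more.
- ρ = .30: r² = .09 / (.4037 × .6111) = .365, worth 57% more.

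Power at d = .30 moves as follows:
- ρ = .05: .468 to .478 in (A); .549 to .566 in (B), where r² = .044.
- ρ = .20: .307 to .379 in (A); .333 to .444 in (B).

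**Step 4: moving the Aim 1 product term to Aim 2 unchanged.** With a free Condition main effect, the product term is a difference in changes. At ρ = .05 its power is .195 in (A) and .244 in (B), below the Implementation-only test. The Baseline data help only as a covariate or through a common Baseline mean.

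**The case against.** **The pooled model is not stated.** Conditions exist only once Implementation begins, Trial design treats Baseline as a separate quasi-experimental comparator, and the technique-use sentence names only a Condition dummy. An Implementation-only reading is at least as natural and has no dilution. This stands. A reader might infer that the Aim 2 estimate is biased toward zero; the article neither says so nor rules it out.

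**At the protocol's own ICC the adjustment is worth almost nothing.** This also stands. The larger gains need ICCs that the article does not give.

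**Chance imbalance is not bias.** A reader might infer that an imbalance in habitual EBT use distorts the randomized contrast. Therapist is a random effect in all models, so that variation is already in the standard error, and an unadjusted Implementation-phase contrast remains unbiased. The matter is precision.

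**Not every therapist has a Baseline value, and not every Aim 2 outcome does.** Of the 32 projected therapists, 4 × 2 = 8 replace dropouts and may join after Baseline. MTFS-I uptake is recorded only during Implementation. Reliability is compared through condition-level ICC_2,2 values and accuracy through equivalence intervals, neither of which a covariate simply enters. It would be wrong to read the point as covering all therapists or all of Aim 2.

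**Baseline data are used elsewhere.** The Phase-by-Condition term is planned, so the data are not unused. But it serves the exploratory Aim 1 contrasts, not the randomized test.

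**An article may leave model detail to an analysis plan.** The covariate sentence is also general: it speaks of examining potential effects and is not labelled as the Aim 2 adjustment set. This lowers the weight of the point but does not remove it, because the article does name the covariates, the model factors, the coefficient that carries the test and the aim to which the product term belongs.

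**Conclusion.** The point holds for technique use, and for therapist-observer discrepancy where it is modelled as a continuous outcome. As written, the Aim 2 Condition test does not adjust for a pre-randomization value of the outcome that the trial collects, and it is not restricted to Implementation-phase data.

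The two parts differ in size. The missing adjustment costs about 3% of variance (1 to 2 power points) at the protocol's ICC of .05, and 23% to 37% only under assumed ICCs of .20 to .30. It will be less to the extent that replacement therapists lack Baseline data. The open choice of phases matters more: a pooled main effect would shrink by 25% to 50%, so that d = .30 becomes .225 or .15, even at ICC .05. That loss is conditional on a pooled fit, which the text permits but does not state. The power figures rest on the assumptions listed with the calculation. The shrinkage factors need only a zero expected Baseline difference and the stated phase weights.

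**What to change.** State that the Aim 2 technique-use contrast is the Condition difference in the Implementation phase. Estimate it with a mixed model on both phases that contains Phase and Phase-by-Condition but no Condition main effect, so that both conditions share one Baseline mean. The product term is then the Baseline-adjusted Implementation difference, and therapists without Baseline data stay in the analysis.

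An alternative is to regress Implementation-phase outcomes on Condition with the therapist's Baseline mean as a covariate, plus a stated rule for missing Baseline values. The two are similar but not equivalent: they treat missing Baseline values, and a noisy mean of two or three sessions, differently.

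Apply the same wording to therapist-observer discrepancy if it is modelled as a continuous outcome. Leave MTFS-I uptake and the ICC_2,2 comparison as they are. No new data are needed; the cost is analysis wording and at most one degree of freedom.
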